**Abbreviations**

CI Confidence interval

DEFF Design effect

DEFFSW Design effect due to stepped-wedge design

DISA District (Manaus)

DST Drug susceptibility testing

FIND Foundation for innovative new diagnostics

FMATM Fundação de Medicina Tropical do Amazonas

GX GeneXpert® MTB/RIF

LACEN Laboratório Central Noel Nutels

MDR Multidrug resistance

MoH Ministry of Health

NTCP National Tuberculosis Control Program

PCF Cardoso Fontes Policlinic

PCR Polymerase chain reaction

PCU Primary Care Unit

PLHA Person living with HIV/aids

QA Quality assurance

SINAN Sistema de Informação de Agravos de Notificação (notification system)

SMS Secretaria Municipal de Saúde (Municipal Health Secretariat)

SOP Standard operating procedure

TB Tuberculosis

WHO World Health Organization

# **I. INTRODUCTION**

Tuberculosis (TB), a preventable and curable disease, persists through the centuries as public health problem worldwide and is an important cause of morbidity and mortality, mainly in developing countries. Despite the existence, for more than 50 years, of efficient antituberculous drugs and an effective treatment to prevent progression of latent TB to active disease, TB is among the ten leading causes of death in the world.[[1]](#endnote-2) In 2009, 9.4 million people had TB and 1.7 million died with TB in the world, of whom 0.5 million living with HIV/aids (PLHA). This represents 4700 daily deaths from TB, which is responsible for ¼ of premature deaths. Among TB, TB causes more deaths than breast cancer and maternity-related conditions.[[2]](#endnote-3)

With these figures, it is not surprising that the United Nations have included among the 8 Millennium Development Goals the control of TB (and other infectious diseases). The goal is to eradicate TB until 2050, decreasing by half the incidence rates.[[3]](#endnote-4) In order to achieve these objectives, the *Union* (International Union Against Tuberculosis and Lung Diseases) proposed, in 1995, the directly observed treatment strategy (DOTS). During one decade, the World Health organization (WHO) widely promoted this strategy and estimated that 8 million deaths were averted. However, in 2005, WHO recognized that the strategy would not be sufficient to attain the millennium goals, and proposed a more comprehensive strategy, the Stop TB Partnership. In a recent review of the intermediate objectives for the 2011-2015 period, the goal was set to detect at least 84% of smear-positive cases and to cure at least 87% of them.Error: Reference source not found

Indeed, the early detection of smear-positive cases and the immediate start of therapy are considered as the most important actions for TB control. Treatment reduces rapidly the number of infectious organisms transmitted by patients thus preventing transmission and the occurrence of secondary cases. In other words, it reduces the number of new patients with TB in the community (incidence) through the cure of prevalent cases. The correct treatment also reduces morbidity, TB-related mortality and drug-resistance.

According to WHO, Brazil has the highest number of TB cases in Latin America and is among the 22 high burden countries, a priority for the disease control, since they concentrate 80% of all TB cases in the world.Error: Reference source not found According to the Brazilian National Information System (SINAN) from the Ministry of Health (MoH), in 2009 72,000 cases were notified, out of the 93,000 estimated by WHO, and 4,700 TB-related deaths occurred in the country. Rio de Janeiro and Amazonas states present the highest incidence rates, 97 and 82 cases per 100,000 inhabitants respectively, corresponding to the double of the national incidence rate. The cities of Rio de Janeiro and Manaus, capitals of Rio de Janeiro and Amazonas states occupy the second and fifth places in the ranking of the highest incidence rates in the country.[[4]](#endnote-5)

The available tuberculosis (TB) diagnostic tools have several limitations: sputum smear examination can be done at the lowest health care levels but has a low sensitivity and therefore two smears usually are examined. Culture is more sensitive and may confirm TB in those with negative smears. Also drug susceptibility testing (DST) requires culturing first. However, culturing and especially DST have a long turnaround time and a higher level of biosafety is required. Rapid PCR methods are available but they require a specialized infrastructure.

In Brazil, smear examinations are widely available for patients with TB suspicion, free of charg for patients, in public health units. Culture is only recommended by the National TB Control Program (NTCP) in patients with previous history of TB, in PLHA, when treatment failure is suspected by the end of the second month of treatment, in difficult to obtain specimens, in extrapulmonary TB and in contacts of a resistant TB index case. Since sputum smear examination has a low sensitivity, the bulk of smear-negative TB diagnoses is made clinically without microbiological confirmation.[[5]](#endnote-6) In addition, despite the official recommendations, according to data from the NTCP, only 72% of new cases and only 17% of retreatment cases perform culture.Error: Reference source not found If added to cases with a negative sputum smear, at present, only one third of Brazil’s notified new cases are bacteriologically confirmed. It is estimated that 20% of these cases are not true TB cases (false positive diagnosis), resulting in delayed diagnosis of the true disease and unnecessary exposure to hepatotoxic antituberculous drugs. In conclusion, the limitations of the currently available tests for TB result in delayed diagnosis and unnecessary treatment.[[6]](#endnote-7),[[7]](#endnote-8)

In order to increase the detection of sensitive TB and to accelerate the diagnosis of resistant TB, the NTCP had the plan, in 2010, to implement universal culture (for every patient suspect of TB). Nevertheless, at present, the national laboratories that perform culture and DST, the state LACENs (Laboratório Central Noel Nutels) cannot absorb this workload, a great investment would be necessary.

A novel test platform has been developed, which is based on rapid real-time PCR. The all-in-one cartridge method allows use outside specialized laboratories. A version for detection of *M. tuberculosis*, the GeneXpert, has been developed with funding by FIND, the Foundation for Innovative New Diagnostics. Controlled trial in over 1700 TB suspects showed a sensitivity of 92.2%, representing a significant gain vis-à-vis sputum smears. In sputum smear negative samples, the sensitivity of GeneXpert® is 72.5% in one sample and reaches 90.2% in three samples.[[8]](#endnote-9)-[[9]](#endnote-10)[[10]](#endnote-11)[[11]](#endnote-12)[[12]](#endnote-13)[[13]](#endnote-14)[[14]](#endnote-15)[[15]](#endnote-16)[[16]](#endnote-17)[[17]](#endnote-18)[[18]](#endnote-19)[[19]](#endnote-20)

This assay also contains primers for the core region of the *rpoB* gene which contains more than 95% of the gene mutations responsible for resistance to rifampicin. Most (≥95%) strains resistant to rifampicin also are resistant to isoniazid.[[20]](#endnote-21) These with multidrug resistant (MDR) TB strains need second-line drugs to be successfully treated. Therefore, rapid detection of rifampicin resistance is important for the patient and prevention of transmission of MDR-TB. This GeneXpert assay has the potential to revolutionize the TB diagnostic process: with its high sensitivity and specificity it can replace smear examination and culture while being applicable in a routine laboratory with minimum infrastructure and limited training levels of staff.

GeneXpert® MTB/RIF is already available in private laboratories in Brazil since 2009, when it was approved by the national regulatory agency ANVISA, equivalent to the USA FDA (DOU supplement Nº 204, Monday, 26 October 2009 - ISSN 1677-7042, attached). Despite the above mentioned evidence of accuracy and potential to reduce diagnosis delay and TB transmission, the Brazilian Unified Health System (SUS) has not yet incorporated this technology, which deprives most of the TB population from its access.

The Government of Brazil and the Bill and Melinda Gates Foundation have entered a high-level agreement for transforming diagnosis and treatment of TB in Brazil. The GeneXpert assay will be validated against culture in Brazil in a study sponsored by FIND. As a complement to the validation protocol, co-developed by FIOCRUZ and FIND and planned to begin in March 2011 (approved by CONEP 630/2010), a study to evaluate cost-effectiveness and potential rollout strategies for GeneXpert assay are presently being proposed in two different protocols. National cost-effectiveness data is required by the Committee for Incorporation of Technologies in Health (CITEC) from the Ministry of Health to allow for the adoption of the GeneXpert assay, providing a basis for evidence-driven policy in this area. This requirement intends to assure that the benefits of incorporating any new technology into the public health system will outweigh the costs needed to make this a reality, i.e., that it has a significant impact on public health at an affordable and justifiable cost. While the validation study will show the potential of the assay, its cost-effectiveness in comparison to existing methods, its size, scope and generalizability will be limited as it will look at test performance and impact on treatment decisions in a limited number of settings.

In order to really demonstrate how the assay should be incorporated in the Brazilian health system, and what level of impact on TB case finding and early appropriate treatment can be expected when applied on a large scale, an expanded pilot introduction is needed. This planned roll-out proposed in the present protocol will also offer the opportunity to complement the planned cost-effectiveness analyses with potential cost savings outside the health system, in particular by incorporating patients’ opportunity costs (separate protocols will be submitted for ethical approval). We therefore propose to assess the potential application for GeneXpert in the Brazilian Health System context as part of a pilot roll out, using a “programmatic cohort” approach that can assess impact. This pilot roll out will be closely monitored and evaluated to document added value and inform broader adoption and roll out in other cities in Brazil.

As it will be afore detailed, the present rollout study proposes a change in the laboratory routine, not in the primary care health units (PCU). Randomization and data analysis will not be individual, but by laboratory/PCU. There is consistent evidence that this change will bring benefits to patients and their contacts, since an early bacteriologically confirmed diagnosis is foreseen, with consequent reduction in transmission. It is expected that this study will provide the NTCP with information for decision making regarding implementation of the technology, necessary personnel training, impact of the test in PCU and laboratory routines and other operational information.

In addition to the increased detection rate, secondary benefits from the substitution of GeneXpert for smears are expected, such as reduction of diagnosis delay of sensitive and drug-resistant TB, of morbidity, mortality and transmission. The reduction in the time to diagnosis of MDR-TB will allow the early treatment with second-line drugs recommended in these cases, also reducing morbidity and mortality, offering less opportunity for MDR-TB transmission. Finally, a reduction in the number of cases erroneously treated as TB is expected. Thus, this project ultimately intends to contribute to TB control in the country.

We emphasize that the present protocol includes only the operational pilot implementation study, other protocol submissions will follow for cost-effectiveness and acceptability studies. The validation study, previously submitted, was approved by CONEP and should be started in March 2011.

# **II. STUDY OBJECTIVES**

## 1. Aim

To improve tuberculosis control in Brazil by increasing the effectiveness of the diagnostic process of pulmonary TB through introduction of novel diagnostic tools.

## 2. Objectives

To estimate, in the routine of public health facilities of two municipalities in Brazil, the impact of the implementation of the GeneXpert assay on

- the case detection of pulmonary TB, measured by the change in rate of notification and treatment registration of bacteriologically confirmed TB, after introduction of the GeneXpert assay as a replacement of sputum smear microscopy in the routine health care settings.
- the detection of MDR-TB

## 3. Expected outcomes

It is expected that the project will provide recommendations to the NTCP regarding changes in the testing algorithm and the potential impact, to inform the sequence of rollout in other states and cities, type of service in which GeneXpert could be used, coverage, acceptability, etc.

The project will support planning, coordination, capacity building, monitoring, equipment and the required supplies for the pilot introduction.

# **III. STUDY POPULATION AND DESIGN**

## 1. Study population

The study will look at the *health system* rather than at individual clinics, i.e. will in both municipalities include a diagnostic center together with all clinics that drain on it. The reason is that introduction of new diagnostics may lead to changes in referral which the study should capture.

In **Rio de Janeiro** there are 10 health districts belonging to the municipal network, each with at least one facility with TB smear examination capacity that serves the other health facilities in the district. If sputum smear examination is requested by the clinic, two specimens are transported to the district microscopy facility for examination. Culture is performed in 4 municipal reference labs: P. Hélio Pellegrino, P. Carlos Alberto Nascimento, H. Municipal Rafael de Paula Souza e H. N. Sra do Loreto. DST is performed in four specialized reference labs that operate outside the Municipal network: Federal University Hospital, Hélio Fraga TB Reference Center, State Lab and Fiocruz. In addition TB is diagnosed in a number of general and emergency hospitals.

Rio de Janeiro has  an estimated population of 6,291,773  in 2008 , and a total TB notification of 7,349 cases among people living in the city (overall notification rate 2008 of 116.8/100,000), including 3,401 Smear-positive pulmonary cases (notification rate 54.1 /100,000), 1,614 smear-negative pulmonary cases (notification rate 25.7/100,000), and 910 extrapulmonary cases (notification rate 14.5/100,000). Of all reported TB cases, 65% are diagnosed by primary care units.[[21]](#endnote-22) In Rio de Janeiro, all 11 laboratories will use the new technology for diagnosisng TB, as detailed in the Methods section.

In **Manaus** there are several basic (primary) care units with TB smear microscopy capacity. The city network is divided into 4 areas, each with a main lab that handles TB diagnostics for the area, but with large variation in numbers of specimens examined and yet limited coordination. Other important diagnostic centers are the Policlinic Cardoso Fontes (PCF) and de Fundação de Medicina Tropical do Amazonas (FMTAM). PCM is the main TB diagnostic center in the city and receives most referrals for TB diagnosis and treatment; it detects 50% of the TB cases in Manaus. FMTAM is an HIV in- and outpatient clinic that handles most TB-HIV co-infection cases. TB culture is done at two sites: LACEN-AM and FMTAM. Manaus in 2008 had an estimated population of 1,73 million, and a smear-positive total TB notification of 1,775: 1,480 pulmonary and 295 extrapulmonary cases (overall notification rate 94/100,000), including 957 (64.7%) smear-positive pulmonary cases 427 smear-negative pulmonary cases (28.9%), and 96 cases in whom no smear test was performed.

During the roll out pilot, the GeneXpert assay will be introduced at each of the 11 laboratories that provide sputum smear microscopy in Rio de Janeiro: this will be the most logical and feasible location for a diagnostic procedure that is to replace smear examination. Since there is no overlap between the health districts in terms of smear microscopy services, this also provides clear separation between allocation units (see Study design, below). This will make calculation of rates based on population denominators straightforward.

In Manaus the GeneXpert assay will be introduced at 3 sites: PCM, FMTAM and one of the 4 TB labs in the city network: the Basic Health Care unit of the Eastern District (Disa Leste). These three sites together take approximately 70% of the current smear examination load in the city. In order to limit overlap in catchment population between these sites and increase coverage of the entire city population, primary care clinics will as much as possible divert, for the duration of the pilot project, their smear examination requests to one of these three sites.

| 2. Study design The design will be a group-based comparison with phased introduction of the GeneXpert (*stepped-wedge* or *phased implementation* design).[[22]](#endnote-23) The units of comparison will be defined as smear examination laboratories together with the clinics that drain upon them for this laboratory service, as defined above. A group-wise comparison is preferred because the intervention will be introduced at the group level (i.e. in laboratories) and the impact of the intervention is thus best assessed at the group level as well. Also, designs with individual comparisons (e.g. individual randomization) will disrupt clinic and laboratory routine and therefore introduce artificial elements that may bias the outcomes (Hawthorne effect).  In this design, all units will start in the *baseline* group, i.e. diagnose TB following current procedures. Each unit will then at different points in time change to the *intervention* group i.e. do GeneXpert instead of smear examination, such that at the end of the observation period all units will be in the intervention group. The sequence by which the units move from baseline to intervention will be randomized. In that way all units will contribute to the person-time observation of both the baseline and the intervention group, but with different durations. This will allow before-after comparison while taking account of potential bias that would be introduced if e.g. case detection rates change over time for reasons not related to the intervention.  See figure 1 for graphic explanation of the design.  *Figure 1. Graphic representation of study design.* | | | | | | | | | |
| --- | --- | --- | --- | --- | --- | --- | --- | --- | --- |
| **Time** | month 1 | month 2 | month 3 | month 4 | month 5 | month 6 | month 7 | month 8 |  |
| **Unit** |  |  |  |  |  |  |  |  |  |
| 1 |  |  |  |  |  |  |  |  |  |
| 2 |  |  |  |  |  |  |  |  |  |
| 3 |  |  |  |  |  |  |  |  |  |
| 4 |  |  |  |  |  |  |  |  |  |
| 5 |  |  |  |  |  |  |  |  |  |
| 6 |  |  |  |  |  |  |  |  |  |
| 7 |  |  |  |  |  |  |  |  |  |
| 8 |  |  |  |  |  |  |  |  |  |
| 9 |  |  |  |  |  |  |  |  |  |
| 10 |  |  |  |  |  |  |  |  |  |
| 11 |  |  |  |  |  |  |  |  |  |
| 12 |  |  |  |  |  |  |  |  |  |
| 13 |  |  |  |  |  |  |  |  |  |
| 14 |  |  |  |  |  |  |  |  |  |
|  | | | | | | | | | |
|  |  | baseline | |  | intervention | |  |  |  |

*Randomization procedure*

Before the start of the study all units will be listed, assigned a random number between 0 and 13 using a random number generator (uniform distribution) and ranked according to the random number’s sequence.

Due to the relatively small number of units, imbalanced randomization with respect to important (confounding) variables is well possible despite randomization. Therefore, we will apply restrained randomization based at least on size of the case load of the laboratories and the estimated HIV prevalence among the patients using the method proposed by Moulton et al.

## 3. Intervention

The intervention will be the introduction of the GeneXpert assay as replacement of sputum smear microscopy in routine health care settings.

During the **baseline period** all patients suspected clinically of pulmonary TB will have sputum smear examination as per routine and current NTCP guidelines, i.e. two sputum samples will be sent with a request form to the microscopy facility. The result is then communicated back to the clinic. In case of one or two positive smear examinations the patient is diagnosed with smear-positive TB and treated accordingly. In case of two negative smears the diagnosis of smear-negative TB is made or rejected on clinical grounds, generally including chest X-ray examination and an assessment of the clinical response to broad-spectrum antibiotics. Repeat smear examination may be done, as may be mycobacterial culture in case the patient qualifies the NTCP selection criteria. Since culture results may take 4 to 8 weeks, the patient may be initiated on treatment before the result becomes available if the clinical condition so requires. A negative culture result then may or may not result in discontinuation of TB treatment.

During the **intervention period** all patients suspected clinically of pulmonary TB will have sputum examination as per routine and current NTCP guidelines, but instead of microscopic smear examination of two specimens, one sputum specimen will be submitted examined using the GeneXpert (Figure 2).The result is then communicated back to the clinic. In case of a positive result the patient is diagnosed with pulmonary TB and treated accordingly. In addition, microscopic sputum smear examination will be done to classify the patient as smear-positive or smear-negative for notification purposes. Note that this will *only be done in case of a positive GeneXpert result* (i.e. for the minority of TB suspects). In case of a positive Genexpert but a negative smear examination, a second sputum specimen will be requested before treatment initiation and examined microscopically in order to fulfill the notification criteria for smear-negative TB (i.e. TB with at least two negative smears).

In case of a negative GeneXpert result but continued clinical suspicion of TB the GeneXpert can be repeated after a time period determined by the clinical condition of the patient.

In case of a positive GeneXpert result with a positive signal for rifampicin resistance the GeneXpert assay will be repeated on a different sputum specimen. If a mutation in the rifampicin resistance-conferring gene is confirmed, the patient will be referred for further evaluation and treatment of MDR-TB as per routine and NTCP guidelines. See for this also the section on ethical considerations. Patients with a confirmed signal for rifampin resistance will be referred to the MDR referral center for further evaluation including culture and DST.

Figure 2: flow chart of laboratorial procedures.

[figure not shown]

## 4. Study endpoints

The study will have the following endpoints:

1. The change in incidence rates of diagnosed and notified bacteriologically confirmed pulmonary TB comparing the baseline to the intervention period, expressed per 100,000 population per annum. We will take the rate of diagnosed TB as well as that of notified TB since the latter is restricted to patients who are put on treatment within the public health system, and data show that 10-15% of the diagnosed cases are not notified. Bacteriological confirmation will be defined as: a positive microscopic smear examination *or* a positive culture with identification positive for *M. tuberculosis,* *or* a positive MTB signal in the GeneXpert assay.
2. The change in incidence rates of diagnosed, but not bacteriologically confirmed, pulmonary TB comparing the baseline to the intervention period, expressed per 100,000 population per annum.
3. The change in incidence rates of diagnosed and notified bacteriologically confirmed (by the GeneXpert) smear-negative pulmonary TB comparing the baseline to the intervention period, expressed per 100,000 population per annum. This is the measure in which the greatest impact is expected.
4. The change in proportion of diagnosed pulmonary TB patients who are ultimately diagnosed as having MDR-TB, comparing patients enrolled in the baseline period with patients enrolled in the intervention period.

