In our calculations C was fixed at 14, λ0 and λ1 were set as indicated below and the additional design effect was varied between 1.5 and 2.0, so that the parameter that changed as a result was y. Assuming fixed population sizes this thus resulted in a minimum observation period for each study arm in a classical group-randomized trial with concurrent allocation of the intervention and equal size, which was then multiplied by 2 to arrive at the total observation period for the stepped-wedge design. We repeated this for total observation periods of 24, 20, 16, 12 and 8 months.

The sample size was calculated based on an average rate of diagnosis of 50/100,000 per annum for the baseline period, and a baseline diagnosis rate of 10/100,000 per annum with bacteriological confirmation through culture (i.e. 20% of sputum smear-negative cases), with a total of 60/100,000 per annum. The minimum diagnosis rate that can then be observed as significantly different from this baseline rate would range from 93/100,000 for a duration of 24 months to 95/100,000 for a duration of 8 months assuming DEFFsw=1.5, and from 110/100,000 for a for duration of 24 months to 112/100,000 for a duration of 8 months assuming DEFFsw=2.0 (figure 2). Varying the average size of the populations served by each unit from 350,000 to 750,000 has very limited effect on these estimates. For a more conservative, “worst case” scenario of a baseline rate of 20/100,000 (i.e. 40% of all smear-negative TB is bacteriologically confirmed in the baseline period), the corresponding figures would range from 109 to 128/100,000, respectively.

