## 10. Data management and analysis

Over the end of the observation period, data from Manaus and Rio will be extracted from SINAN and GAL as described above. The routine procedures to check errors and linkage will be performed by the designated units in the Health Department, as per routine. This procedure includes checking for duplication, suspected incompatibilities, scale errors. Units are then informed. In Rio, [name] is responsible for this routine. In Manaus, by the municipal TCP manager, [name]. Once this procedure and linkage is done, the identification variables will be deleted and the following variables will be retained for analysis:

- From both SINAN and GAL: patient code, age, sex, health district of residence, sputum smear and culture resultsError: Reference source not found
- From SINAN only: clinic of notification, diagnostic classification (smear-positive/smear-negative/extrapulmonary), treatment history (new, previously treated), date of diagnosis, date of treatment initiation, HIV status, other major co-morbidities.
- From GAL only: positive sputum smear examination details (number of positive smears, highest smear grade obtained, date(s), laboratory); positive mycobacterial culture (number of positive cultures, identification, date(s), laboratory); drug susceptibility results (DST done yes/no, results for each drug tested, date(s), laboratory); positive GeneXpert (number of assays done; highest value obtained; rifampicin resistance yes/no/indeterminate, date(s), laboratory).

General data cleaning will be performed, including checks for duplicate entries, suspected mismatches, range errors, and results communicated to the responsible surveillance units for updating.

The patient code will be assigned for the analysis only and have no reference to patient identifiers.

The data analysis will be performed using STATA and will include:

- 1. Calculation of the number of diagnosed, bacteriologically confirmed pulmonary TB cases by smear status, for each unit, separately for baseline and intervention period.
  2. Calculation of the number of notified pulmonary TB cases, irrespective of bacteriological confirmation, by smear status and in various strata of age, sex and HIV status, for each unit, separately for baseline and intervention period.

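### Endpoint 3 counts only GeneXpert-confirmed smear-negative TB, so its baseline rate is a structural zero, contrary to the protocol's own confirmation rule and culture-confirmed planning baseline of 10/100,000

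*Protocol*

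**What the plan says.** All references are to the protocol, part III.

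- **Study endpoints, endpoint 3** compares the incidence rate of diagnosed and notified "bacteriologically confirmed (by the GeneXpert) smear-negative pulmonary TB comparing the baseline to the intervention period". The protocol expects its greatest impact on this measure.
- **Study endpoints, endpoint 1** defines bacteriological confirmation more widely: a positive smear, or "a positive culture with identification positive for" *M. tuberculosis*, or a positive GeneXpert signal.
- **Study design** has all units start at baseline, where they "diagnose TB following current procedures". GeneXpert begins only when a unit crosses over.
- **Intervention** allows culture of smear-negative patients at baseline: repeat smear may be done, "as may be mycobacterial culture in case the patient qualifies the NTCP selection criteria". In the intervention period smear follows only a positive GeneXpert: "microscopic sputum smear examination will be done to classify the patient as smear-positive or smear-negative for notification purposes".
- **Sample size** assumes "a baseline diagnosis rate of 10/100,000 per annum with bacteriological confirmation through culture", which is 20% of the smear-negative cases.
- **Data management and analysis** counts confirmed cases by smear status without restricting the confirming test (items 1 and 3). Item 2 is "Calculation of the number of notified pulmonary TB cases, irrespective of bacteriological confirmation, by smear status". Item 4 gives rate ratios and rate differences; item 5 is a Poisson regression of the rate ratios.

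**The concern.** A before-after comparison needs a case definition that can be met in both periods. The parenthesis in endpoint 3 ties the definition to a test that exists in only one of them. Apart from contamination, the baseline numerator is then empty whatever the true amount of confirmed smear-negative TB.

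Two things are at stake. First, a rise in this endpoint would not separate additional confirmed cases from cases that culture already confirmed and GeneXpert now labels instead. Second, the quantity named as the endpoint is not the one the study was sized on, so the power statement does not apply to it. The argument for an 8-month study is that it can detect roughly a doubling of confirmed smear-negative TB, and a doubling of zero has no meaning.

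**Working it through.** **Inputs (Sample size; Study duration and phasing).** C = 14 units; 500,000 inhabitants per unit; k = 0.25; z values 1.96 and 0.84, multiplied by DEFFsw of 1.5 or 2.0; total duration 8 or 24 months, half of it in each condition. Diagnosed pulmonary TB is 100/100,000 per annum, half of it smear-positive. That leaves 50 smear-negative, of which 20% are culture-confirmed: 50 × 0.20 = 10/100,000.

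**Formula in the protocol**

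C = 1 + f × [(λ0 + λ1)/y + k²(λ0² + λ1²)] / (λ0 − λ1)², with f = (2.80 × DEFFsw)²

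At 8 months, y = 500,000 × 4/12 = 166,667 person-years per unit and condition. f = 17.64 at DEFFsw 1.5 and 31.36 at DEFFsw 2.0.

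**Step 1: reproduce the stated figures.** Solving for λ1 (per 100,000 per annum):

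| λ0 | DEFFsw | 24 months | 8 months | Protocol states |
|---|---|---|---|---|
| 60 | 1.5 | 92.83 | 94.47 | 93 and 95 |
| 60 | 2.0 | 109.23 | 111.69 | 110 and 112 |
| 10 | 1.5 | 16.14 | 17.55 | 17 and 18 |
| 10 | 2.0 | 19.21 | 21.37 | 20 and 22 |

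Rounded up, all eight agree. The sentence on smear-negative cases calls 17 to 22 an increase and repeats the total of 60. The figures match only as detectable levels from λ0 = 10: the detectable increase from 60 at 24 months and DEFFsw 1.5 would be 93 − 60 = 33. The ratios at 8 months, 17.55/10 = 1.8 and 21.37/10 = 2.1, are the protocol's approximate doubling. So the protocol's own calculation counts culture-confirmed cases at baseline.

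**Step 2: the same formula under the literal endpoint (λ0 = 0).** It reduces to λ1 = 1 / {y × [(C − 1)/f − k²]}.

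- DEFFsw 1.5: 13/17.64 − 0.0625 = 0.6745; λ1 = 1/(166,667 × 0.6745) = 0.89/100,000.
- DEFFsw 2.0: 13/31.36 − 0.0625 = 0.3520; λ1 = 1/(166,667 × 0.3520) = 1.70/100,000.

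For unit populations from 750,000 down to 350,000 the range is 0.59 to 2.43/100,000. The stated 18 to 22 therefore cannot belong to the endpoint as written.

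**Step 3: illustration with no true gain.** Assume GeneXpert finds exactly the 10/100,000 that culture confirms, and nothing else.

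- Person-years per condition: 14 × 500,000 × 4/12 = 2.33 million.
- Expected cases: 2.33 million × 10/100,000 = about 233 in each condition; true ratio 1.
- Literal endpoint 3 compares 0 with about 233.
- Chance of significance by the protocol's formula at DEFFsw 2.0: variance term 10⁻⁴/166,667 + 0.0625 × 10⁻⁸ = 1.225 × 10⁻⁹; √(13 × 10⁻⁸ / 1.225 × 10⁻⁹) = 10.30; 10.30/2.0 − 1.96 = 3.19, a power of about 99.9%. It is higher at DEFFsw 1.5.

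**Step 4: what the planned analyses would do.** With an empty baseline the rate ratio is undefined and the Poisson coefficient has no finite estimate, so a Wald test need not be significant. An exact two-sided comparison of 0 with n at equal person-time has p = 2 × 0.5ⁿ: 0.0625 at n = 5 and 0.031 at n = 6. Six cases would suffice before clustering is allowed for; DEFFsw raises that number.

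**The case against.** The strongest reply is that the parenthesis is a slip the rest of the protocol does not follow. Endpoint 1 counts culture, the sample size counts culture, and analyses 1 and 3 do not restrict the test. No endpoint is designated primary, and endpoint 1, with one rule for both periods, still answers the first objective. Most of this stands. It makes the point an internal contradiction rather than proof that a comparison with zero is intended. It does not remove the contradiction: if culture is meant to count, the listed analysis does not implement the endpoint as defined.

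Three stronger readings are tempting, and the documents do not support them.

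- *A significant result is guaranteed.* It is near certain on a difference or exact test, but the planned rate ratio and Poisson model break down with an empty period.
- *All unconfirmed smear-negative cases, 50 − 10 = 40/100,000, lose their smear class after the switch.* That is a ceiling. The Intervention section gives every GeneXpert-positive patient a smear, and a second if the first is negative. Assuming the Introduction's 20% false diagnoses and 72.5% one-sample sensitivity apply here, 40 × 0.8 × 0.725 = about 23 would keep a class and about 17 would not, before any repeat GeneXpert. Those 17 still count in endpoint 2, which ignores smear status.
- *Every table by smear status is compromised, including the MDR-TB analyses (7, 10 and 11).* Among confirmed cases only GeneXpert-negative, culture-positive patients lack a smear, and no harm to the MDR-TB analyses can be shown from the text. The exposure lies mainly in analysis 2.

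**Conclusion.** The point holds as a contradiction in the endpoint definition. As written, endpoint 3 has a structural zero at baseline, while the confirmation rule and the sample size for the same quantity include culture at 10/100,000. The detectable level at 8 months is 17.6 to 21.4/100,000 with culture counted and 0.9 to 1.7/100,000 without it. Under the literal wording the planned ratio is not estimable, and a difference or exact test says almost nothing about added confirmation.

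The 233-versus-0 figure is an illustration. It rests on the protocol's planning inputs, four months per condition, and the assumption that GeneXpert finds only what culture finds. It is not a forecast. The zero also assumes no GeneXpert results reach baseline units from elsewhere, such as the private laboratories mentioned in the Introduction.

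The correction is small but needed, because the protocol expects the greatest impact on this measure.

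**What to change.** 1. Redefine endpoint 3 as diagnosed and notified pulmonary TB confirmed by culture or GeneXpert and not smear-positive, with the same rule in both periods. This is the quantity the sample size already uses.
2. Report the count confirmed by GeneXpert alone descriptively, for the intervention period only.
3. Show GeneXpert-negative, culture-positive patients of the intervention period as a separate line, and add a sensitivity analysis excluding them. They have no smear, so some who would have been smear-positive at baseline enter the new class and raise the intervention count. Excluding them errs the other way, since it also removes truly smear-negative cases. If culture is requested on the same criteria in both periods, the two results bracket the comparison.
4. In analysis 2, show notified cases with no smear as their own category, and do not compare smear-negative notifications between periods without it.

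The cost is one sentence in the endpoint, one extra category in analysis 2, one extra line and one sensitivity analysis. Smear, culture and positive GeneXpert results are already among the variables extracted from SINAN and GAL. The remaining downside is the misclassification in item 3, which can be shown but not removed while smear follows only a positive GeneXpert.
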